#### Secondary Outcomes

In the COVID-19 quarantined group, the severity of obsessive-compulsive symptoms, evaluated through the OCI-R, the perceived loneliness and suicidal ideation will be considered as secondary outcome measures.

In the COVID-19+ patient group, the severity of post-traumatic symptoms at the Severity-of-Acute-Stress-Symptoms-Adult scale will be considered. The hypothesis is that post-traumatic symptoms are more severe in this group compared to the other ones.

In the COVID-19 health staff group, the presence of burn-out symptoms, in particular mental exhaustion, and suicidal ideation will be considered. We anticipate that first-line professionals will report higher levels of mental exhaustion and suicidal ideation compared to second-lines staff members.

In the COVID-19 mental health group, the secondary outcome measures will include the adoption of maladaptive coping strategies (e.g., drinking alcohol) and a poor resilience style. Patients with pre-existing mental disorders are expected to adopt more maladaptive coping strategies and poorer resilience styles compared to the other three groups.

#### Exploratory Outcomes

The use of Internet and social media will be tested as possible moderator of the impact of pandemic and quarantine (**Figure 1**). Moreover, the exposure time to COVID-19 and to the related containment measures will be tested as possible mediators of the severity of the clinical symptomatology. Finally, the other exploratory outcomes will include the variety of coping strategies and resilience styles as well as the different levels of post-traumatic growth.

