### Data Analysis

Statistical analyses will be conducted according to a multistep plan. Missing data will be handled using the multiple imputation approach (47). Descriptive statistics will be calculated for the dependent and confounding variables. A bilateral alpha of 0.05 is considered, and error and confidence intervals are calculated at 95%.

The analytic plan will include: 1) data cleaning of the online dataset and replacement of missing values; 2) descriptive statistics of the general characteristics of the recruited sample, in terms of levels of depressive and anxiety symptoms, post-traumatic and stress-related symptoms, insomnia, satisfaction with life, suicidal ideation, hopelessness, post-traumatic growth, resilience, coping strategies, and social support; 3) sub-groups analyses based on the level of exposure to the pandemic (i.e., COVID-19 quarantine group vs. COVID-19+ patients group vs. COVID-19 healthcare staff group vs. COVID-19 mental health group); 4) calculation of a propensity score, in order to adjust our findings for the likelihood of being exposed to the pandemic and to the quarantine (48, 49). This method is adopted since it produces a better adjustment for differences at baseline, rather than simply including potential confounders in the multivariable models. The independent variables used for calculating the propensity score will include gender, age, socio-economic status, and geographical region. The obtained propensity score will be used to weight the observations in the multivariable analyses. In the final regression model, the inverse probability weights, based on the propensity score, will be applied in order to model for the independence between exposure to the pandemic/quarantine and mental health outcomes and estimation of causal effects (48, 49); 5) development of a Structural Equation Model (SEM), in order to evaluate the possible role as mediators and moderators of coping strategies, post-traumatic growth and usage of social networks on the severity of depressive and anxiety symptoms, post-traumatic and stress-related symptoms, suicidal ideation, and hopelessness.

In order to improve the external validity and generalizability of our findings, all analyses will be controlled for the impact of confounding variables, such as age, gender, and geographical region.

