We believe that our study has several strengths, which should be highlighted. First, this is the first national multicentric, no-profit study carried out in Italy with a rigorous methodology for evaluating the impact of pandemic and quarantine on mental health. Second, the development of a web-based platform for data collection will give us the opportunity to recruit a high number of participants. Based on previous population surveys carried out in Italy, an ideal target would have been 10,000 participants, but this target has been reached in only 7 days. Therefore, we expect to reach more than 20,000 people within the study period. A third relevant strength of our study is the selection of validated and reliable assessment instruments, which are available and validated in several languages. The next step of the project will be to adapt our survey to the European level, by involving several countries. Fourth, several psychopathological dimensions will be evaluated, not only those usually assessed following natural disasters, such as the post-traumatic and depressive-anxious dimensions. In this study, we will also evaluate the obsessive-compulsive spectrum, the suicidal ideation, the maladaptive use of Internet, among the others, which represent novel targets for psychiatrists (73, 74).

Our study has obviously also some limitations. In particular, the study sample includes the adult population only, due to existing restrictions related to the provision of informed consent of children and adolescents in Italy. However, it is likely that the pandemic will have a detrimental impact on the mental health of adolescents as well (75, 76). Moreover, being exposed to a traumatic event during early life is associated with alterations in the social, emotional, and cognitive development and could determine a variety of impairment in the adulthood. The effects of the pandemic on children and adolescents will be evaluated in an *ad hoc* study, in which we will explore the relationship between parents and their underage children during the pandemic. Another limitation is related to the recruitment process, which might partially bias our findings, since only persons interested in the topic of the survey may have voluntarily participated. However, we expect that most people are interested in participating in the survey given the global magnitude of the current traumatic threat with collective psychological and social reactions.

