Another possible limitation of our study is the choice to use a web-based online survey, which may have limited the participation of people not having access to the Internet or not familiar with online tools, particularly the elderly. The cross-sectional design of the study does not allow an evaluation of changes over time as regards the levels of severity of symptoms. However, in order to overcome this possible bias, we will compare our findings with those already available from the Italian population (46) and will adopt a propensity score approach in order to understand the impact of the duration of exposure to the pandemic on the risk of developing psychiatric symptoms. With this methodology, we will be able to evaluate the levels of post-traumatic growth and the type of resilience styles in the study population in order to identify possible critical areas to be targeted in the post-acute phase. However, these psychological constructs are slow to change, and this is why we will promote a second wave of the survey, which will start six months after the end of the “lockdown phase” in Italy. Finally, the survey link can be used multiple times in order to allow sharing and re-posting it. This methodological choice could bias the findings, since the same person can potentially compile the survey several times. However, this methodological choice was due to the adoption of the “snowball” sampling, and it is rather unlikely that someone can compile the same long survey more than once.

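### Exposure time is a mediator in one section and the exposure of interest in another, and the mediation paths planned in step 5 cannot be identified from a single cross-sectional survey

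*Protocol article*

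**What the plan says.** The protocol article assigns roles to the same variables in three places.

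- **Exploratory Outcomes:** "the exposure time to COVID-19 and to the related containment measures will be tested as possible mediators of the severity of the clinical symptomatology". Internet and social media use is a moderator only. Coping, resilience and post-traumatic growth are exploratory outcomes.
- **Data Analysis:** step 3 describes "sub-groups analyses based on the level of exposure to the pandemic", with the four groups as the levels. Step 4 plans the "calculation of a propensity score, in order to adjust our findings for the likelihood of being exposed to the pandemic and to the quarantine", so exposure to the pandemic or quarantine is the cause. The step 5 structural equation model (SEM) is to "evaluate the possible role as mediators and moderators of coping strategies, post-traumatic growth and usage of social networks". Exposure time is not in that list, and social-network use may now be a mediator as well as a moderator.
- **Discussion, limitations:** the authors "will adopt a propensity score approach in order to understand the impact of the duration of exposure to the pandemic", which makes duration the exposure whose effect is wanted.

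The design is cross-sectional, and every instrument is self-reported in one online survey. The limitations concede that change in symptom severity over time cannot be evaluated. They offer an external Italian comparison, the propensity score and a second survey wave six months after lockdown. They do not extend the concession to mediation.

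**The concern.** A mediator has to be caused by the exposure and has to come before the outcome. Time spent under containment is an amount of the exposure, and the article names no earlier variable whose effect it would carry to symptoms. An analyst could not tell from the three sections whether to model it as a cause, as an intermediate or not at all.

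The step 5 mediators raise a second problem. Coping, growth and social-network use are recorded at the same moment as depression, anxiety and stress. People with worse symptoms may cope differently because of them. One survey cannot separate that direction from the one the model assumes, and with more than 20,000 respondents expected, even a weak reverse path would probably reach significance and be read as an indirect effect.

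**Working it through.** The article gives no mediation effect or power figure, so there is nothing of its own to reproduce. Two checks apply.

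**1. What time under containment can be.** Inputs: lockdown declared 8 March and measures prolonged to 4 May (Background); survey open 30 March to 30 June 2020 (Recruitment Procedure). Assumption: duration is counted in calendar days from 8 March and stops at 4 May. The article does not define it.

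- At survey opening: 8 to 30 March = 22 days.
- At the end of containment: 8 March to 4 May = 57 days.
- Possible values: 57 − 22 + 1 = 36.
- Survey length: 2 + 30 + 31 + 30 = 93 days. After 4 May there remain 27 + 30 = 57 days, and everyone answering then has the same value, 57.

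So defined, the variable is a function of response date. Response date is not among the propensity score variables (gender, age, socio-economic status, region).

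On spread: the Discussion says of the 10,000 target that "this target has been reached in only 7 days". If those were the first 7 survey days, up to 10,000 / 20,000 = half of the expected minimum sample has values of 22 to 28 days, that is 7 of 36. This limits the precision of a dose-response analysis. It does not measure the mediation problem.

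**2. What a single-wave mediation model returns when the order is reversed.** Assumptions, none from the article: standardised exposure X, symptoms Y = 0.3X + noise, coping M = cY + noise. Coping is then a consequence of symptoms and the true indirect effect is 0. The fitted model assumes X → M → Y.

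- Path X to M: a = 0.3c.
- Path M to Y given X: b = (c − 0.3 × 0.3c) / (1 − 0.09c²) = 0.91c / (1 − 0.09c²).
- Apparent indirect effect: ab = 0.273c² / (1 − 0.09c²), to be compared with a total effect of 0.3.

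The formula agrees with a simulation of 200 runs per setting (Sobel test, two-sided alpha 0.05):

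| c | ab by formula | Share of total | Simulated ab, N = 20,000 | Significant, N = 20,000 | Significant, N = 10,000 |
|---|---|---|---|---|---|
| 0.1 | 0.00273 / 0.9991 = 0.0027 | 0.9% | 0.0027 | 98.5% | 80.5% |
| 0.3 | 0.02457 / 0.9919 = 0.0248 | 8.3% | 0.0246 | 100% | 100% |
| 0.5 | 0.06825 / 0.9775 = 0.0698 | 23.3% | 0.0701 | 100% | 100% |

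When the data are generated in the assumed order (X to M 0.3, M to Y 0.3, direct effect 0.2), the same method recovers the truth: 0.0899 against 0.3 × 0.3 = 0.09. The estimate is therefore right or spurious according to an ordering that the survey cannot test. Weighting by a propensity score built on gender, age, socio-economic status and region does not supply that ordering.

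**The case against.** The case on the other side has real weight, and several stronger readings that a reader might infer do not survive it.

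- **That the mediation results would be wrong.** Not shown. They are unidentified, and correct if the assumed order holds. The article gives no basis for the size or direction of any bias.
- **That exposure time can never be a mediator.** Too strong. The sentence also covers time of exposure to the virus, and a path from group (first-line staff, for example) through that time to symptoms is conceivable. It is not specified. Figure 1 may show the intended structure but cannot be seen here.
- **That duration equals calendar days since 8 March.** This is an assumption. People could leave home for work, health or urgent needs, so individual exposure to the measures may vary.
- **That listing coping and growth as outcomes contradicts their use as mediators.** It does not, because a mediator is itself an outcome of the exposure.
- **That reverse causation is likely throughout.** The Discussion says of growth and resilience that "these psychological constructs are slow to change", which makes them less likely to be products of recent symptoms. The same remark weakens the path from a weeks-old exposure to growth, and it does not cover coping or social-network use.
- **That the choice of intervention targets rests on the SEM.** No section says so. Next Steps adapts modules to the characteristics and needs of the four groups and then plans a randomised trial.

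It is also fair that the wording is tentative (possible mediators, possible role) and that the cross-sectional limit is partly conceded. What remains is the conflict of roles between sections and the absence of any ordering for the step 5 mediators.

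**Conclusion.** The point stands in a limited form. Exploratory Outcomes, Data Analysis and the limitations give exposure time incompatible roles: mediator, absent from the SEM, and exposure of interest. For time under the national measures, a mediation test has no coherent meaning, because that time is a dose. If counted from 8 March, it runs from 22 to 57 days and is largely set by when a person responded. Social-network use also changes role between Exploratory Outcomes and step 5.

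The indirect effects planned in step 5 are not identified from the first survey. Under the stated illustrative assumptions, a true indirect effect of zero would appear as about 1% to 23% of the total effect and would be declared significant in 98.5% to 100% of runs at N = 20,000. Those percentages depend on the assumed coefficients and do not predict this study's bias.

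The reach is confined to the exploratory and SEM analyses. The primary DASS-21 comparison is not touched. The sections should be reconciled before analysis, because the change alters what the study may claim from these models.

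**What to change.** 1. In Exploratory Outcomes, stop calling time under containment a mediator. Define it as exposure or dose: days from 8 March to submission, capped at 4 May. Analyse it for dose-response with the covariates already planned, and state that it is tied to response date.
2. Bring Data Analysis and the limitations into line with that role. If time of exposure to the virus is meant to carry an effect of group, write that path out.
3. Give social-network use one role in both Exploratory Outcomes and step 5.
4. In step 5, report first-survey SEM paths for coping, post-traumatic growth and social-network use as associations, claiming no indirect or causal effects. Relabelling growth as a moderator would be no remedy, since growth may itself follow the exposure.
5. Reserve mediation for the second wave, and only if respondents can be linked. The article does not state any linkage, and the survey link is reusable.

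Cost: wording only, with no new data in the first survey. Downside: no mediation claim from the first wave, and possibly none at all if linkage is not feasible.

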**Figure 1 f1:**
[figure not shown]
Determinants of mental health during the COVID-19 pandemic.

### Data Analysis

Statistical analyses will be conducted according to a multistep plan. Missing data will be handled using the multiple imputation approach (47). Descriptive statistics will be calculated for the dependent and confounding variables. A bilateral alpha of 0.05 is considered, and error and confidence intervals are calculated at 95%.

The analytic plan will include: 1) data cleaning of the online dataset and replacement of missing values; 2) descriptive statistics of the general characteristics of the recruited sample, in terms of levels of depressive and anxiety symptoms, post-traumatic and stress-related symptoms, insomnia, satisfaction with life, suicidal ideation, hopelessness, post-traumatic growth, resilience, coping strategies, and social support; 3) sub-groups analyses based on the level of exposure to the pandemic (i.e., COVID-19 quarantine group vs. COVID-19+ patients group vs. COVID-19 healthcare staff group vs. COVID-19 mental health group); 4) calculation of a propensity score, in order to adjust our findings for the likelihood of being exposed to the pandemic and to the quarantine (48, 49). This method is adopted since it produces a better adjustment for differences at baseline, rather than simply including potential confounders in the multivariable models. The independent variables used for calculating the propensity score will include gender, age, socio-economic status, and geographical region. The obtained propensity score will be used to weight the observations in the multivariable analyses. In the final regression model, the inverse probability weights, based on the propensity score, will be applied in order to model for the independence between exposure to the pandemic/quarantine and mental health outcomes and estimation of causal effects (48, 49); 5) development of a Structural Equation Model (SEM), in order to evaluate the possible role as mediators and moderators of coping strategies, post-traumatic growth and usage of social networks on the severity of depressive and anxiety symptoms, post-traumatic and stress-related symptoms, suicidal ideation, and hopelessness.

In order to improve the external validity and generalizability of our findings, all analyses will be controlled for the impact of confounding variables, such as age, gender, and geographical region.

Data will be stored in an online dataset by the coordinating center. For safety reasons, the dataset will be protected by a two-step password. It will be possible to export data in compatible formats with common calculation software (e.g., Microsoft Access and Excel) and in specific softwares (e.g., SPSS and STATA) for the statistical analyses.

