### Data Collection

#### Recruitment Procedure

An online survey has been set up through EUSurvey, a web platform launched in 2013 by the European Commission. The application, hosted at the Department for digital services (DG DIGIT) of the European Commission, is available to all EU citizens at https://ec.europa.eu/eusurvey. The survey will be online from March 30 to June 30, 2020 (https://ec.europa.eu/eusurvey/runner/COVIDSurvey2020). The survey takes approximately 15–30 min to be completed. Participants can stop the survey at any time and save their answers as “draft” on the web-platform. Furthermore, participants can interact with the principal investigator of the study and with all researchers through email messages at any time during and after study participation.

Participants will be subdivided into four groups: a) Group 1—COVID-19 quarantine group. This group includes the general population which are quarantined but not isolated, i.e., those not directly exposed to contagion nor in contact with COVID-19+ individuals; b) Group 2—COVID-19+ group, which includes isolated people directly/indirectly exposed to the virus; c) Group 3—COVID-19 healthcare staff group, which includes first- and second-line healthcare professionals; d) Group 4—COVID-19 mental health, which includes users of mental health services and all those who had already been diagnosed with a mental disorder.

The survey addresses the Italian population aged over 18 years through a multistep procedure: 1) email invitation to health professionals and their patients; 2) dissemination of the link through social media channels (Facebook, Twitter, Instagram) and the mailing lists of national psychiatric associations; 3) involvement of national associations of stakeholders (e.g., associations of users/carers); 4) official communication channels (e.g., university websites; websites of the hospitals directly involved in the management of the pandemic).

The invitation letter includes information on study purposes and confidentiality. The provision of the informed consent is mandatory in order to start the survey.

The snowball sampling procedure—without the definition of strict inclusion/exclusion criteria (except that of age limit)—will give us the opportunity to recruit a large sample of the Italian population and to evaluate the effect of the studied variables on the outcome measures.

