## Discussion

Our survey will give us the opportunity to describe the impact of the pandemic on the mental health of different subgroups of the Italian population.

In fact, the analyses will be run according to the four subgroups of respondents: the general population not directly affected by the virus (COVID-19 quarantine group); people who have had a direct or indirect contact with the virus (COVID-19+ patients group); those working in health care units as first or second-line staff (COVID-19 healthcare staff group); people with mental health problems, independently from the contact with the virus (COVID-19 mental health). This choice is due to the evidence that stress and traumas have a different impact on different target groups (7, 50–52).

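### The four groups combine virus contact, occupation and prior diagnosis, overlap with one another, and are analysed as levels of exposure, so worse scores in Group 4 cannot be attributed to pandemic exposure

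*Protocol article*

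**What the plan says.** The protocol article defines the groups under Recruitment Procedure, and the Abstract repeats the definitions:

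- Group 1: "the general population which are quarantined but not isolated, i.e., those not directly exposed to contagion nor in contact with COVID-19+ individuals".
- Group 2: "which includes isolated people directly/indirectly exposed to the virus".
- Group 3: "which includes first- and second-line healthcare professionals".
- Group 4: "which includes users of mental health services and all those who had already been diagnosed with a mental disorder".

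Recruitment has no eligibility criterion other than age, so nothing at entry keeps the groups apart.

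The Discussion describes two of the groups differently. Group 2 becomes "people who have had a direct or indirect contact with the virus (COVID-19+ patients group"), with no mention of isolation. Group 4 is "people with mental health problems, independently from the contact with the virus (COVID-19 mental health"), and the later Discussion paragraph on this group repeats that independence.

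Step 3 of Data Analysis nevertheless plans "sub-groups analyses based on the level of exposure to the pandemic" and names all four groups as those levels. Primary Outcome ranks the groups on DASS-21, with first-line and second-line staff in different positions and Group 4 highest. Under Secondary Outcomes, "Patients with pre-existing mental disorders are expected to adopt more maladaptive coping strategies and poorer resilience styles compared to the other three groups".

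**The concern.** The grouping variable carries the between-group hypothesis on the primary outcome and several secondary hypotheses. If it mixes exposure, occupation and psychiatric history, a difference between groups cannot be assigned to any one of them.

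Group 4 is the clearest case. People with a prior mental disorder would plausibly score higher on DASS-21, and show poorer coping and resilience, without a pandemic. Calling the group a level of exposure invites the difference to be read as an exposure gradient. The other contrasts are affected less directly: the means of Groups 1 to 3 depend on where respondents who meet several definitions are placed.

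**Working it through.** **1. Do the definitions overlap or leave gaps?** Cross three contact/isolation states with staff (no/yes) and prior diagnosis (no/yes): 3 × 2 × 2 = 12 profiles. Every respondent is taken as quarantined, and isolation as occurring only in exposed people. The groups met under the Recruitment Procedure wording are:

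| State | Neither | Diagnosis only | Staff only | Staff and diagnosis |
|---|---|---|---|---|
| No contact, not isolated | 1 | 1, 4 | 1, 3 | 1, 3, 4 |
| Contact, not isolated | none | 4 | 3 | 3, 4 |
| Contact, isolated | 2 | 2, 4 | 2, 3 | 2, 3, 4 |

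Four profiles fit one group, five fit two, two fit three and one fits none.

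Under the Discussion wording of Group 2 (any contact), the middle row becomes 2; 2, 4; 2, 3; 2, 3, 4. Then three profiles fit one group, six fit two, three fit three and none is left out. The looser wording closes the gap, but it contradicts the Methods and raises the overlapping profiles from 7 to 9. These counts are of profiles, not of respondents.

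**2. Is Group 4 a level of exposure?** Step 3 says so by listing it. The Discussion says membership does not depend on contact with the virus. Both cannot hold.

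**3. Does the rest of the plan separate prior disorder from exposure?**

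- The listed propensity variables are gender, age, socio-economic status and geographical region. The confounders named at the end of Data Analysis are age, gender and region. Prior disorder is in neither list.
- Adding it would not rescue a four-group contrast. Everyone in Group 4 has a psychiatric history by definition, and if Group 4 takes precedence nobody elsewhere does, so there is no common support.
- The only unexposed comparator named under Primary Outcome is a community sample, not one of people with mental disorders.
- The Discussion concedes that the cross-sectional design cannot show change over time.

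**4. Illustration of size.** The article gives no SD, effect size or group sizes, only an expected total above 20,000. There is no stated figure to reproduce, and every input below is assumed.

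*Placement of overlapping staff.* Shift in the Group 3 mean = share with a prior diagnosis × their excess in SD. With 5–20% and 0.3–1.0 SD, this runs from 0.05 × 0.3 = 0.015 SD to 0.20 × 1.0 = 0.20 SD. The difference detectable with 80% power at two-sided 0.05 is (1.960 + 0.842) × √(2/n):

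| n per group | Detectable difference (SD) |
|---|---|
| 500 | 0.177 |
| 1,000 | 0.125 |
| 2,000 | 0.089 |
| 5,000 | 0.056 |

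The shift is negligible at the low end and as large as a detectable contrast at the high end.

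*Group 4 with no pandemic effect at all.* Probability of a significant difference = Φ(d√(n/2) − 1.960). With a pre-existing gap of d = 0.2 SD and n = 500 per group, d√(n/2) = 3.162, so Φ(1.202) = 0.885. With d = 0.5 it exceeds 0.999. At n = 1,000 and d = 0.2 it is 0.994.

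**The case against.** A journal article condenses the full protocol, and a rule for respondents who meet two definitions is the kind of detail it omits. That stands: a reader might infer that assignment is arbitrary, but all that can be said is that it is not fixed in this article. The Discussion also hints that Group 4 takes precedence over Groups 1 and 2. Applying that hint to the table still leaves five overlapping profiles: one in Groups 1 and 3, one in Groups 2 and 3, and three in Groups 3 and 4. If general population in Group 1 is also read as excluding staff, four remain.

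Other stronger readings are tempting and are not supported:

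- *The authors treat Group 4's top rank as proof of pandemic impact.* The article does not say so. Primary Outcome tests impact against the unexposed community sample, and the group ordering is a separate statement.
- *One four-level variable enters the causal model.* Step 3 is a subgroup analysis. Step 4 models exposure to the pandemic or quarantine without saying how it is coded.
- *The Group 4 contrasts have no use.* The second aim is to find intervention targets for different categories of people, and Next Steps tailors modules to the four groups. Group descriptions serve that aim.
- *Some people are necessarily unclassified.* This is true under the Methods wording only.
- *Pooling contacts with infected people dilutes the Group 2 hypothesis by a known amount.* That hypothesis is stated for the group, the share infected is not given, and no listed item shows that infected respondents can be told apart from contacts.

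The contradiction over Group 4, the disagreement over isolation in Group 2 and the mixing of three axes all remain. They are matters of what the article states, and a separate analysis plan would not remove them.

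**Conclusion.** The concern holds in this form. The groups rest on three non-exclusive axes. Step 3 labels all four as exposure levels although the Discussion defines Group 4 independently of contact. The Methods and Discussion disagree on whether Group 2 requires isolation. As written, the DASS-21 ranking confounds exposure with occupation and prior disorder, and worse DASS-21, coping or resilience scores in Group 4 than in the other groups cannot be attributed to pandemic exposure.

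This conclusion rests on the definitions, the listed adjustment variables and the cross-sectional design, not on assumed figures. The size of any bias cannot be calculated from the document. The SD figures show only that it could range from negligible to decisive. With more than 20,000 respondents expected, sampling error will be small, so misattribution is the larger risk.

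**What to change.** 1. Reconcile the Group 2 definitions in the Methods and Discussion, stating whether isolation is required and where a non-isolated contact belongs.
2. In the between-group and weighted models, code three separate factors and enter them together: contact/isolation status, healthcare role (none, second-line, first-line, as the Primary Outcome hypothesis requires) and pre-existing mental disorder (no, yes).
3. Treat pre-existing disorder as a stratifier or as an effect modifier of contact status, not as an exposure level. Reword step 3 to match.
4. Keep the four groups for descriptive tables and intervention planning.
5. Report the post-traumatic outcome separately for infected respondents and contacts, if the survey items allow it.

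The cost is some recoding of information already needed to form the groups, one interaction term and smaller strata. The change does not supply a pre-pandemic baseline for people with a prior disorder, so the main effect of that factor still cannot be read as pandemic impact. It does allow contact and occupation to be estimated with prior disorder held constant, and shows whether the association with contact differs by prior disorder.
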